## Statistics and data analysis

### Sample size and assumptions

The exploratory trial of the intervention 
[15] showed a difference of weight change between baseline and 8 weeks of 1.41 kg (SD = 1.9) between the intervention and control groups. As the trial population may be more heterogeneous, and the outcome is measured 4 weeks later, we powered the study to detect a mean difference in weight change of 1.0 kg, with a standard deviation of 2.5. Based on a two sample test, 132 evaluable participants per arm are required to detect such a difference with 90% power, and a significance level of 5%. This sample size has been calculated using the statistical software STATA. However, a clustering effect may occur in the intervention arm due to different health professionals delivering the intervention in each practice. Power calculation formulae for a partially clustered design have been reported 
[42]. Based on an average cluster size of 13 evaluable participants (those completing 3 months follow-up), and an ICC of 0.05 
[43] in the intervention arm, a total of 364 evaluable patients at 3 months (26 in each of the 14 practices) would provide 92% power to detect such a difference. This should insure the power stays above 90% even with a small imbalance in cluster size between practices 
[44]. Allowing for 30% attrition (26% observed in the pilot study at 8 weeks), 260 participants would need to be recruited by arm, or 520 in total.

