### Data analysis

Baseline characteristics will be reported by each arm using descriptive statistics. A random effects linear regression model accounting for clustering by health professionals delivering the intervention in the intervention arm will be used to compare the weight change at 3 months from baseline between the two groups. This analysis will be adjusted for baseline weight which should make the statistical analysis more efficient. Random effects linear regression model will also be used to investigate the clustering effects due to practice.

Bias due to missing data will be investigated. If required, sensitivity of the results to missing data will be investigated using different approaches for handling missing data, including adjusting for predictors of missingness that are related to the outcome, multiple imputation and baseline observation carried forward. The possibility that data may not be missing not at random (MNAR) will also be considered and if necessary approaches that can handle MNAR data will be used as part of the sensitivity analysis 
[45]. Additionally, the scope of incorporating information on reasons for dropout in the analyses will also be explored.

Secondary outcomes will be compared between the intervention groups using appropriate regression models taking account of clustering. Subgroup analyses will investigate intervention effects by gender, age (in tertiles), baseline BMI (<35 vs. ≥35), ethnic origin (white vs. other) and deprivation (tertiles of postcode-based Index of Multiple Deprivation) as part of secondary analyses. Results from all secondary analyses will be considered as exploratory.

The primary aim of the trial is to evaluate the effectiveness of offering the intervention; therefore all analyses will be performed on an intention to treat basis. A detailed analysis plan will be prepared nearer the data analysis stage.

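### Effect modification by age, BMI and deprivation is specified only in categories, which leaves information unused if the modification is roughly linear

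*Protocol article*

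**What the plan says.** The Data analysis section of the protocol article names five subgroup factors. Three of them have an underlying continuous or finely graded scale: "Subgroup analyses will investigate intervention effects by gender, age (in tertiles), baseline BMI (<35 vs. ≥35", and "deprivation (tertiles of postcode-based Index of Multiple Deprivation". The other two, gender and ethnic origin (white against other), are treated as categories and are not at issue here.

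The same section classes all secondary results as exploratory and defers detail to a later analysis plan. It does not say which test of effect modification will be used, and it neither plans nor rules out an analysis on the continuous scale.

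The ungrouped values exist. Under Demographics, date of birth and post code are collected at baseline. Under Anthropometric measures, BMI is calculated from measured weight and height.

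**The concern.** A treatment-by-covariate interaction on the continuous scale uses every participant's value on 1 degree of freedom. Replacing the value by a tertile or a two-way split treats everyone within a group as alike. If the effect changes steadily with age, BMI or deprivation, the variation within groups carries information that the grouped analysis does not use.

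The trial has little power to spare for this question. It is sized for the main effect: "we powered the study to detect a mean difference in weight change of 1.0 kg, with a standard deviation of 2.5". Interactions are estimated less precisely than main effects, so an avoidable loss of efficiency bears directly on whether effect modification could be seen. For age and deprivation there is a lesser drawback: the tertile boundaries depend on who is recruited and from which 14 practices, which makes comparison with other trials harder.

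**Working it through.** **1. The plan's own figures.**
- Per arm, unclustered: n = 2 × 2.5² × (1.960 + 1.282)² / 1.0² = 131.3, rounded up to 132. This agrees with "132 evaluable participants per arm are required to detect such a difference with 90% power, and a significance level of 5" percent, taken as two-sided.
- With clustering in the intervention arm only (13 per cluster, ICC 0.05, 182 per arm): the design effect is 1 + 12 × 0.05 = 1.6. SE = √(6.25 × 1.6/182 + 6.25/182) = 0.299, and power = Φ(1/0.299 − 1.96) = 91.7%. The article says 364 evaluable patients "would provide 92% power to detect such a difference".
- Attrition: 364/0.7 = 520.

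All three reproduce, and none depends on the subgroup analyses.

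**2. Measure of loss.** For a linear interaction in a randomised comparison, the share of information kept by grouping is the between-group variance of the covariate divided by its total variance. The loss is one minus that share. The article gives no distribution for age, BMI or deprivation, so every shape below is an assumption.

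**3. Tertiles (age, deprivation).**

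| Assumed shape | Loss |
|---|---|
| Uniform | 1/9 = 11% |
| Truncated normal, age 18 to 85 (underlying mean 52, SD 14) | 18% |
| Normal: 1 − 6φ(0.431)² = 1 − 0.793 | 21% |
| Lognormal (log-SD 0.5) | 32% |
| Exponential | 35% |

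With equally spaced trend scores, the two skewed shapes lose 35% and 39%.

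**4. BMI split at 35, entry at 30 or more.** Take BMI = 30 + an exponential variable with mean m, and let p = exp(−5/m) be the share at 35 or above. The share of information kept is [p/(1 − p)] × 25/m².

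| Mean BMI | p | Kept | Loss |
|---|---|---|---|
| 33 | 0.189 | 0.647 | 35% |
| 34 | 0.287 | 0.627 | 37% |
| 35 | 0.368 | 0.582 | 42% |
| 36 | 0.435 | 0.534 | 47% |
| 37 | 0.490 | 0.489 | 51% |

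Less skewed shapes lose somewhat less. Truncated normals with means of 33.3 to 37.1 lose 34% to 43%. Shifted gammas with means of 35 and 36 lose 39% to 45%.

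**5. Effect on power.** For 80% power on 1 df the noncentrality is (1.960 + 0.842)² = 7.85. Multiply it by the share kept:
- Normal tertiles, 1-df trend: Φ(√(7.85 × 0.793) − 1.96) = 70%.
- Normal tertiles, 2-df test (noncentral chi-square, noncentrality 6.22): 60%.
- BMI split keeping 55% to 60% (skewed BMI, mean 35 to 36, SD about 4 to 5): Φ(√(7.85 × 0.55) − 1.96) = 55%, and Φ(√(7.85 × 0.60) − 1.96) = 58%. Other shapes near those means run from 53% (exponential, mean 36) to 62% (truncated normal, mean 35.3).

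**6. What such an interaction means in kilograms.** With SD 2.5 and 364 evaluable, ignoring clustering, the SE of the interaction per SD of the covariate is 2 × 2.5/√364 = 0.262 kg. The interaction detectable with 80% power is 2.80 × 0.262 = 0.73 kg per SD. Against a mean effect of 1.0 kg, this implies about 0.27 kg at one SD below the mean and 1.73 kg at one SD above.

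For tertiles, about 61 per arm per tertile gives an SE of 2.5 × √(2/60.7) = 0.454 kg for each effect and 0.454 × √2 = 0.642 kg for top minus bottom. The detectable difference is therefore 1.80 kg. For a normal covariate the top and bottom tertile means lie 2.18 SD apart, so 0.73 kg per SD corresponds to 1.60 kg. The ratio (1.60/1.80)² = 0.79 recovers the share kept in step 3.

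**7. Weaker interactions.** Starting from 20% power on the continuous scale, normal tertiles give 17% (1 df) or 13% (2 df), and the BMI split gives 13% to 14%. At 0.25 kg per SD, continuous power is only about 16%.

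**The case against.** The strongest reply is that this belongs to the analysis plan. The article names groupings but no test, promises a detailed plan, and labels the results exploratory. That limits the weight of the point but does not remove it: the groupings are written down, and a plan that follows the article would carry them forward.

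Several stronger readings are tempting and are not supported:
- **That the loss is a known figure.** It rests on linear modification and on distributions the article does not give. If the effect changed in a step near BMI 35, the planned split would lose little or nothing.
- **That the data are thrown away.** The ungrouped values are kept, and a continuous analysis stays open.
- **That tertiles commit the trial to a 2-df test, or to reading each subgroup on its own.** The text says neither, and a 1-df trend across tertiles fits it equally well.
- **That all the cut-points depend on the sample.** The BMI cut is fixed in advance.

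The power comparison starting from 80% also presumes a large interaction, 0.73 kg per SD against a 1.0 kg target. For small interactions the gain is a few percentage points. That objection stands, and the size of the point should be read accordingly.

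**Conclusion.** The point holds as a modest improvement to exploratory analyses; it is not an error in the plan. The article specifies effect modification by age, BMI and deprivation only in categories although all three are available ungrouped. Given roughly linear modification, about 10% to 50% of the information on the interaction goes unused. The low end is tertiles of an evenly spread covariate, and the high end is the BMI split in a skewed population with mean BMI near 37. For an interaction large enough to have 80% power on the continuous scale, the cost is about 10 to 25 percentage points of power, depending on the covariate and the test. For weaker interactions it is much smaller. The article does not show which of these assumptions the recruited sample will meet. The primary comparison and the sample size do not depend on any of this.

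**What to change.** In the analysis plan, state that effect modification by age, baseline BMI and deprivation score will each be tested by adding a treatment-by-continuous-covariate interaction to the primary model, linear in the covariate, with a spline check of the shape. Keep the stated tertiles and the BMI split at 35 for displaying estimates, so that no planned output is lost. Gender and ethnic origin stay as they are, and the results remain exploratory.

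The cost is a sentence or two of wording and no new data. The downside is a linearity assumption. The spline check examines it, though with limited power at this sample size, so the displayed category estimates remain a useful companion.

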### Economic analyses

Economic analyses will conform to NICE’s preferred methodology 
[46]. The costs of the intervention will be calculated using a bottom-up method. Within-trial quality adjusted life years (QALYs) gained during the follow-up period will be derived from EQ-5D scores measured throughout the trial until two years. Predicted lifetime QALYs gained will be estimated using decision-analytic modelling to predict long-term quality adjusted survival and costs. Cost-effectiveness will be measured in terms of incremental cost per unit change in body weight and per QALY gained (using both within-trial and lifetime QALYs). Results will be subjected to simple and probabilistic sensitivity analysis.

### Analysis of qualitative interviews

All interviews will be audio recorded and transcribed. Thematic analysis will be used to identify the main themes that will form the basis of our results.

## Data storage and retention

Data management will be handled by PRIMENT Clinical Trials Unit with data being held according to Good Clinical Practice (GCP) requirements. As per GCP requirements, data will be held for a minimum of ten years from completion of the project.

## Ethical approval, research governance and data access

Ethical approval was obtained from the South East London Research Ethics Committee 2 via IRAS, (Ref No. 10/H0802/59, Approval granted 9th July 2010) with other participating centres providing site-specific approval as per normal IRAS procedures. NHS Research and Development (R&D) approval was obtained from all participating NHS Boards prior to the start of the trial. Further advice and support on governance and GCP issues will be provided by PRIMENT Clinical Trials Unit, who provide Standard Operating Procedures for tasks such as obtaining consent, managing and archiving data, access to trial data, training and how to handle breaches of GCP. The trial has been submitted to the International Standard Randomised Controlled Trials (ISRCT) and allocated the number ISRCTN16347068.

## Study/trial sponsorship

University College London is the sponsor of this trial.

## Discussion

The 10TT intervention is consistent with Foresight’s recommendations which include *promoting healthier food choices, building physical activity into our lives,* and *personalised advice and support*[2]*;* complementing preventive care with treatment for those who already have weight problems.

Obese patients have regular contact with primary care even before experiencing any specific obesity-related co-morbidities 
[47]; providing an opportunity for early intervention. However, weight management activities in primary care are limited and inconsistent 
[48], with some GPs reluctant to raise the subject of weight 
[49], and many lacking confidence in existing treatments 
[50]. The 10TT intervention addresses these issues, offering a simple, low-cost, treatment that can be delivered by primary care staff without special expertise.

Existing reviews identify a need for novel, practical, empirically supported trials with adequate follow-up 
[8,48,51,52]. Many ongoing or recently completed behavioural clinical trials registered with the metaregister of controlled trials (mRCT) focus on interventions with high levels of therapeutic contact (e.g. counselling, tailored interventions, variable content over time). These interventions show promise for use with patients who are willing to engage in a therapeutic programme but may not be as acceptable to those with more limited interest in weight control. The habit-formation approach could complement these by providing a low-contact alternative. Evidence of better weight loss maintenance for self-guided than professionally-led programmes 
[53] is also supportive of this approach.

The results from this study will assess the impact of the 10TT intervention on body weight over 3 months and will provide information on whether the weight loss is maintained up to 24 months. It will also increase understanding of whether the focus on habit formation leads to improvements in, and increased automaticity of, diet and physical activity behaviours, and if it is cost-effective in the NHS context. If proven to be effective when delivered through primary care, 10TT could make a highly cost-effective contribution to improvements in population health.

## Abbreviations

10TT: 10 Top Tips; EQ-5D: EuroQol −5 domains; GCP: Good clinical practice; GPRF: General Practice Research Framework; ISRCT: International Standard Randomised Controlled Trials; LDL: Low-density lipoprotein; LOCF: Last-observation-carried-forward; mRCT: metaregister of controlled trials; MNAR: Missing not at random; NHS: National Health Service; NICE: National Institute for Health and Clinical Excellence; QALYs: Quality adjusted life years; R&D: Research and Development.
